4.6.1 Prohibited concomitant medications

1. Other anticholinergics
2. Tricyclic antidepressants

Subjects who have discontinued any of these medications must have a wash-out period of 14 days and can be enrolled in the study.

4.6.2 Concomitant medications to be used with care

1. Alpha blockers (which have been stably used for more than one month prior to the start of the study)
2. 5-alpha reductase inhibitors (which have been stably used for more than two months prior to the start of the study)

Patients who are on any of those concomitant medications must continue to take them during the study.

# **5. Treatment**

5. 1. Treatment administration

Treatment: Vesicare®

Posology: One 5 mg or 10 mg tablet to be taken before sleep

The Vesicare tablet should be swallowed whole without being chewed or crushed.

5. 2. Permitted concomitant therapy

All drugs other than those specified as unauthorized drugs are allowed during the study.

5. 3. Non-permitted concomitant therapy

Electrostimulation and magnetic therapy

# **6. Evaluation of the Study Drug**

All efficacy endpoints, except the BSW questionnaire, are compared with baseline.

6. 1. Primary efficacy endpoint

- Changes in micturition frequency on the voiding diary (Appendix 1) (from baseline to end of study)

6. 2. Secondary efficacy endpoints

- PPBC (changes from baseline to week 12)
- OABSS (changes from baseline to week 12)
- BSW questionnaire at week 12

6. 3. Safety endpoints

General clinical safety will be assessed based on data on spontaneously reported adverse events at each visit. To this end, subjects will be asked: “Since last visit*,* have you had any unusual symptoms or any health problems you had never experienced before?”

- Adverse events
- Changes in maximum flow rate (MFR) measured by uroflowmetry (from baseline to week 12)
- Changes in post-void residual (PVR) urine volume assessed by bladder scan (from baseline to week 12)

According to the recommendations of the International Consultation on BPH, the PSA will be measured at baseline. Normal laboratory ranges will be provided in the CRF.

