# **7. Practical Conduct of the Study**

7. 1.Visit 0 (days -21 to 0)

- An oral explanation of the clinical trial to subjects.
- Dating and signing of the informed consent form by subjects
- Collection of necessary information including demographics, disease history, clinical history and associated conditions and relevant concomitant medications.
- Physical examinations including a digital rectal exam in male subjects.
- Laboratory tests: Urinalysis, CBC, chemistry and serum PSA (only in male subjects)
- PPBC and OABSS assessments
- Uroflowmetry and residual urine assessment
- A voiding diary is explained and given to each subject.
- Identification of concomitant medications

7. 2.Visit 1 (day 0)

- Laboratory test results are confirmed.
- Subjects for the clinical trial are selected based on the inclusion and exclusion criteria after an evaluation of their voiding diaries.
- Subjects are prescribed one Vesicare 5 mg tablet to take before sleep for four weeks. The tablet should not be chewed, divided or crushed.
- Concomitant medications are identified.
- The voiding diary is given to each subject.

7. 3. Visit 2 (week 4)

Visit 2 will take place four weeks after the inclusion visit (or if necessary, within seven days before or after the theoretical date).

- Adverse events are identified.
- The date when each subject took the study drug is confirmed.
- The voiding diary is evaluated.
- The PPBC and OABSS questionnaires are evaluated.
- Subjects are prescribed one 5 or 10mg Vesicare 5 mg or 10 mg tablet to take before sleep for eight weeks. The tablet should not be chewed, divided or crushed. Dose escalation to 10 mg is determined after consultation between the investigator and subjects.
- Concomitant medications are identified.
- The voiding diary is given to each subject.

7. 4. Visit 3 (week 12)

Visit 3 will take place eight weeks after the inclusion visit (or if necessary, within seven days before or after the theoretical date).

- Adverse events are identified.
- The date when each subject took the study drug is confirmed.
- The voiding diary is evaluated.
- The PPBC and OABSS questionnaires are evaluated.
- Concomitant medications are identified.
- Uroflowmetry and residual urine assessment
- Patient satisfaction with the study drug is assessed by the BSW questionnaire.

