# **8. Adverse Events**

8. 1. Definition

8. 1. 1. Definition of adverse events

“Any unfavorable or unintended sign, symptom or disease occurring in subjects in association with the use of an investigational medicinal product and which does not necessarily have a causal relationship with the investigational drug. ”

In particular, any abnormal laboratory finding or sign which leads to treatment discontinuation is to be considered as an adverse event.

8. 1. 2. Definition of serious adverse events

A serious adverse event is any untoward medical occurrence or adverse drug reaction that at any dose of an investigational drug:

- results in death or is life-threatening;
- requires hospitalization or prolongation of existing hospitalization
- causes a persistent or significant disability or incapacity.
- results in a congenital anomaly or birth defect; or
- is associated with any other medically important condition. .

8. 2. Procedures

8. 2. 1. Notification and documentation of adverse events

Any adverse event should be documented on the patient chart and reported on the case report form (CRF).

8. 2. 2. Notification and documentation of serious adverse events

If any serious adverse event is found during the study (V0 to V2), the investigator must report the occurrence of such event immediately or **within one working day** to Astellas Korea by phone or fax, using Astellas’ standard SAE report form.

- In any case, the report must show the identity of the investigator and be dated and signed. It should also give an assessment of the causal relationship between the event and the study drug.

8. 2. 3. Procedures during and after the study

The investigator should follow up and monitor patients for the outcome of clinical adverse events or abnormal laboratory findings until recovery or stabilization of their condition.

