# **9. Drop-out**

9. 1. Reasons for drop-out

Patients may drop out of the study at any time, for whatever reason, once they decide to do so, or the investigator may decide to withdraw patients from the study. All dropouts must be documented and the investigator must specify the reasons (e.g., failure of a patient to pay a visit despite receipt of notice, lack of cooperation from the patient, lack of treatment efficacy, worsening of the clinical condition obstructing continued compliance with the protocol, occurrence of adverse events ...).

9. 2. Procedures

- All dropouts must be recorded on the patient chart and CRF.
- If any event causing a drop-out meets the definition of serious adverse events, the investigator will carry out the procedures as described in section 8.2.
- For patients lost to follow-up, the CRF must be completed until the date the last visit took place. The investigator will use his/her best effort to find out the reason why a patient failed to pay the visit, if any, and to determine the state of his/her health.

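### The only scripted adverse-event question depends on symptoms being unusual or new, which is narrower than the protocol's adverse-event definition and may under-capture known symptoms that return or worsen

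*Protocol*

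**What the plan says.** Section 6.3 sets out how safety is collected: "General clinical safety will be assessed based on data on spontaneously reported adverse events at each visit". For that purpose it gives one question, covering the time since the last visit: "have you had any unusual symptoms or any health problems you had never experienced before". No other adverse-event question is scripted. Sections 7.3 and 7.4 list, for visits 2 and 3, only that "Adverse events are identified".

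The definition is in section 8.1.1: "Any unfavorable or unintended sign, symptom or disease occurring in subjects in association with the use of an investigational medicinal product", whether or not the drug caused it. The section adds that "any abnormal laboratory finding or sign which leads to treatment discontinuation is to be considered as an adverse event". Neither sentence asks that the event be new or unusual for the patient. Section 8.2.1 requires every adverse event to be entered on the chart and the case report form.

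Worsening is named in section 9.1, where one of the example reasons for drop-out is "worsening of the clinical condition obstructing continued compliance with the protocol".

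**The concern.** The definition and the question do not cover the same events. The definition takes in any unfavorable or unintended sign, symptom or disease. The question filters by whether the patient finds the symptom unusual or has never had the problem before. A symptom that the patient already knows can meet the definition and still not fit the question.

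Adverse events are one of three listed safety endpoints, beside maximum flow rate and residual urine. Laboratory tests are scheduled at visit 0 only, so after baseline the planned safety data are those two measurements and whatever patients report. The wording of the one prompt therefore matters. An event that is never elicited cannot be recovered in the analysis, so a statistical analysis plan could not repair this.

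**Working it through.** The documents give no adverse-event rate, no share of previously treated patients and no share of recurrent events, so there is no figure to reproduce. The check is a comparison of the texts.

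1. **Scope of the definition (8.1.1).** Any unfavorable or unintended sign, symptom or disease in association with use of the product. Novelty is not required. Worsening and recurrence are not named; they fall within it because of its breadth.

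2. **Scope of the question (6.3).** It has two limbs joined by *or*: unusual symptoms, and health problems never experienced before. The second limb excludes anything the patient has had before. The first is ambiguous: marked worsening might strike a patient as unusual, but a familiar symptom that returns might not.

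3. **Difference.** Known symptoms that return or worsen can lie inside the definition and outside the question. The protocol itself admits three kinds of patient to whom this applies:
   - *Mild past constipation.* Exclusion criterion 16 bars only chronic constipation or a past severe form. A patient with milder earlier episodes can enter, and a further episode is not a first.
   - *Side effects known from earlier treatment.* After listing other anticholinergics and tricyclic antidepressants, section 4.6.1 says: "Subjects who have discontinued any of these medications must have a wash-out period of 14 days and can be enrolled in the study". Such a patient may already know the side effects of these drugs.
   - *Worsening within the trial.* Sections 3 and 7.3 allow escalation from 5 mg to 10 mg at week 4, and section 3 foresees patients who cannot tolerate the higher dose. A symptom that began before visit 2 and worsened afterwards is no longer new at visit 3. This case arises in either group and needs no assumption about earlier treatment.

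4. **Other routes of capture.** The instruction to identify adverse events at visits 2 and 3 gives no other wording. The duty in 8.2.1 applies once the investigator knows of an event. Section 9.1 records worsening when it leads to drop-out. None of these is a prompt to a patient who remains in the study with a known symptom that has become worse.

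**The case against.** The strongest reply is that section 6.3 supplies a prompt and does not say that only answers to it count. Investigators must identify adverse events at both visits and document all of them. Section 8.2.3 has them follow known events until recovery or stabilization, so a symptom reported at visit 2 should still be under observation at visit 3. Flow rate and residual urine are measured whatever the patient says. The limb on unusual symptoms may draw out marked worsening, and volunteered reports are not barred.

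Much of this stands. It means that such events may be under-captured, not that they are lost. A reader might go further and infer that previously treated patients are in effect told to withhold known side effects; nothing in the text tells them so. A reader might also call the question a contradiction of section 8.1.1. It is narrower than the definition, but the definition does not name worsening or recurrence and the question does not alter it.

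The reply does not remove the gap. The general duties depend on the event coming to light, and the one prompt written to bring it to light depends on novelty.

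**Conclusion.** The point holds as a mismatch of scope: the scripted question is narrower than the definition it serves, and recurrence or worsening of known symptoms may be under-captured. It rests on two readings: that the breadth of 8.1.1 includes such events, and that some patients would not call a familiar symptom unusual.

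The size cannot be determined from the documents. A reader might infer that group 2, as the overactive bladder group, holds more previously treated patients and would therefore look safer than it is. The protocol does not support that. Section 4.6.1 applies to both groups, no share of previously treated patients is given for either, and the Introduction suggests that many frequency-only patients may themselves be overactive bladder cases. If both groups had the same true event rate *p*, and shares *s1* and *s2* of their events went unreported as already known, the recorded rates would be *p*(1 − *s1*) and *p*(1 − *s2*), a gap of *p*(*s2* − *s1*). The gap is zero when the shares are equal and changes sign when they are exchanged; *p*, *s1* and *s2* are all unknown here. Nor does the protocol state a between-group test of adverse events: section 10.3 names only the analysis set.

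This is an inexpensive improvement to safety capture. It does not affect the primary efficacy analysis.

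**What to change.** Replace the question in section 6.3, and any matching text in the case report form, with an open, non-leading one that does not depend on novelty and covers return and worsening. For example: *Since the last visit, have you had any new symptom or health problem, or has any you already had come back or become worse?*

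Judge the answers against the definition in 8.1.1. Do not add a rule that every increase over the history taken at visit 0 is an adverse event: change in micturition frequency is the primary efficacy endpoint, and such a rule would count worsening of the study condition as both an efficacy result and an adverse event.

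The cost is one sentence in the protocol, the matching form text if there is any, and slightly more events to record. The disease and clinical history already taken at visit 0 gives a reference for what each patient had before treatment, so no new baseline assessment is needed.

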6.4 Other

A blood chemistry examination, hematologic test and PSA (only in male) will be performed at baseline.

# **7. Practical Conduct of the Study**

7. 1.Visit 0 (days -21 to 0)

- An oral explanation of the clinical trial to subjects.
- Dating and signing of the informed consent form by subjects
- Collection of necessary information including demographics, disease history, clinical history and associated conditions and relevant concomitant medications.
- Physical examinations including a digital rectal exam in male subjects.
- Laboratory tests: Urinalysis, CBC, chemistry and serum PSA (only in male subjects)
- PPBC and OABSS assessments
- Uroflowmetry and residual urine assessment
- A voiding diary is explained and given to each subject.
- Identification of concomitant medications

7. 2.Visit 1 (day 0)

- Laboratory test results are confirmed.
- Subjects for the clinical trial are selected based on the inclusion and exclusion criteria after an evaluation of their voiding diaries.
- Subjects are prescribed one Vesicare 5 mg tablet to take before sleep for four weeks. The tablet should not be chewed, divided or crushed.
- Concomitant medications are identified.
- The voiding diary is given to each subject.

7. 3. Visit 2 (week 4)

Visit 2 will take place four weeks after the inclusion visit (or if necessary, within seven days before or after the theoretical date).

- Adverse events are identified.
- The date when each subject took the study drug is confirmed.
- The voiding diary is evaluated.
- The PPBC and OABSS questionnaires are evaluated.
- Subjects are prescribed one 5 or 10mg Vesicare 5 mg or 10 mg tablet to take before sleep for eight weeks. The tablet should not be chewed, divided or crushed. Dose escalation to 10 mg is determined after consultation between the investigator and subjects.
- Concomitant medications are identified.
- The voiding diary is given to each subject.

7. 4. Visit 3 (week 12)

Visit 3 will take place eight weeks after the inclusion visit (or if necessary, within seven days before or after the theoretical date).

- Adverse events are identified.
- The date when each subject took the study drug is confirmed.
- The voiding diary is evaluated.
- The PPBC and OABSS questionnaires are evaluated.
- Concomitant medications are identified.
- Uroflowmetry and residual urine assessment
- Patient satisfaction with the study drug is assessed by the BSW questionnaire.

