| **Study population and Number of study centers** | Expected number of subjects enrolled: 286 patients  Number of subjects expected to complete the study : 256 patients (128 in each group), considering a10% drop-out rate  Duration of medication: 3 months  Number of centers: 9 centers |
| --- | --- |
| **Statistical analysis** | Efficacy analysis will be performed in FAS and PP sets, whereas safety analysis will be conducted in those patients who have taken the study drug at least once.  - Primary efficacy assessment  A t-test will be used to compare changes in frequency of urination (from baseline to the end of the study) between study groups on the voiding diary (see Annex 1) and calculate a 95% confidence interval for the difference between the groups. Further analysis, if necessary, will be conducted with a generalized linear model in order to correct heterogeneity between the groups.  - Secondary efficacy assessment  Secondary efficacy endpoints (i.e., PPBC, OABSS and BSW) will be analyzed using the the Wilcoxon signed-rank sum test or paired t-test for continuous data and the McNemar test for categorical data. If necessary, a mixed effect model or generalized estimation equation will be used as an analysis tool to test the difference between study groups. |
| **Expected study duration** | Patient screening begins in February 2009.  The last patient enrollment is completed by the end of June 2009. |

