# Study Schedule

|  | V0  (Days -21 to 0) | V1  (Day 0) | V2  (Week 4 ± 7 days) | V3  (Week 12 ± 7 days) |
| --- | --- | --- | --- | --- |
| (baseline) * | |
| Informed consent | **●** |  |  |  |
| Demographics | **●** |  |  |  |
| Medical history, associated  diseases | **●** |  |  |  |
| Laboratory test:  CBC  Chemistry**  Urinalysis  PSA (only in male)*** | **●**  **●**  **●**  **●** |  |  |  |
| Voiding diary dispensed | **● ****** | **●** | **●** |  |
| Voiding diary collected |  | **●** | **●** | **●** |
| PPBC | **●** |  | **●** | **●** |
| OABSS | **●** |  | **●** | **●** |
| Flow rate (Uroflowmetry) | **●** |  |  | **●** |
| Residual urine (Bladder scan) | **●** |  |  | **●** |
| BSW questionnaire |  |  |  | **●** |
| Prescription |  | **●** | **●** |  |
| Compliance |  |  | **●** | **●** |
| Adverse events |  |  | **●** | **●** |
| Concomitant medications | **●** | **● ******* | **●** | **●** |

Intervals between different visits: ± 7 days

* Screening tests should be performed and confirmed prior to prescription at V1.

** Chemistry: AST, ALT, BUN, Cr, ALP, T-bil

*** PSA leves should be measurements within the last 3 months (replaceable by data from other institutions).

**** Voiding diary should be kept for 3 days prior to V1, V2 and V3.

***** Any prohibited drugs must not have been taken for at least 2 weeks prior to V1.

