# **3. Description of the Study**

This study is an open-label, multi-center, observational, comparative trial conducted for three months by nine urologists in South Korea.

This study is also a non-inferiority study hypothesizing that the effect of solifenacin is not inferior in patients with frequency only to others with both frequency and urgency.

Principal investigator: [name], University of Ulsan Asan Medical Center

Co-investigator: [name] [name], Inha University Hospital

Co-investigator: [name] [name] (co-investigator), Keimyung University Dongsan Medical Center

Co-investigator: [name] [name], Korea University Hospital

Co-investigator: [name] [name], Pusan National University Hospital

Co-investigator: [name] [name], Daegu Catholic University Hospital

Co-investigator: [name], Samsung Medical Center, Sungkyunkwan University

Co-investigator: [name], Chungnam National University Hospital

Co-investigator: [name] [name], Chonnam National University Hospital

In this study, the screening period is from week 0 to week 3. Patients included in the trial will receive one tablet of solifenacin succinate (5 mg or 10 mg) for a period of three months.

This study will involve four planned visits: pre-inclusion visit (V0), inclusion visit (V1), 1 intermediate visit (V2, 4-week intervals) and end-of-study visit (V3, week 12).

If needed, visits may take place within 7 days before or after the theoretical dates calculated from V1.

Demographics include body weight, age, sex, education level, occupation and parity (for female only). Patients are asked to keep a 3-day voiding diary at baseline and at weeks 4 and 12 after initiation of treatment.

Patients are divided into two groups: group 1 (frequency without urgency) and group 2 (frequency with urgency). Both of the groups receive solifenacin succinate over a period of 12 weeks.

- At the beginning, patients receive solifenacin succinate 5 mg.

- At week 4, they can have the dose escalated to 10 mg after consultation with the investigator.

- If there are patients who are not able to withstand the new dose after dose escalation, it can be reduced back.

Uroflowmetry and residual urine measurement will be performed at baseline and week 12.

Patients will be asked to complete the PPBC and OABSS questionnaires at baseline and at weeks 4 and 12 of treatment. At the end of the study, they will be asked to complete the BSW questionnaire.

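### Prescriptions of four plus eight weeks do not cover the late end of the ±7-day visit windows, so some permitted week-4 and week-12 diary days fall after the prescribed treatment ends

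*Protocol*

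**What the plan says.** - **Prescription.** Section 7.2 (V1): "Subjects are prescribed one Vesicare 5 mg tablet to take before sleep for four weeks". Section 7.3 (V2) prescribes a 5 mg or 10 mg "tablet to take before sleep for eight weeks".
- **Total duration.** Section 3: "Both of the groups receive solifenacin succinate over a period of 12 weeks". The Synopsis has "Duration of medication: 3 months", and section 3 also speaks of three months.
- **Visit windows.** Section 3: "If needed, visits may take place within 7 days before or after the theoretical dates calculated from V1". The Study Schedule words it differently: "Intervals between different visits: ± 7 days". Sections 7.3 and 7.4 repeat the 7-day allowance.
- **Diary timing.** Study Schedule footnote: "Voiding diary should be kept for 3 days prior to V1, V2 and V3".
- **Use of the diary.** Section 6.1 makes the change in diary frequency the primary endpoint. Section 2.1 states the objective as change to week 12 of treatment. Under sections 10.2 and 10.3, the last post-baseline value is carried forward (LOCF) for patients who withdraw.
- **V3 date.** Section 7.4, under a week-12 heading, places V3 eight weeks after inclusion.

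**The concern.** The diary is tied to the visit date, and the visit may move. The prescription is a fixed length. The protocol neither extends treatment to a late visit nor ties the diary to days on drug. Following the stated durations and windows to the letter can therefore place primary-endpoint diary days after treatment has ended, which is not what the objective describes.

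The direction matters because this is a non-inferiority comparison. If similar shares of both groups lose some of the effect before the diary is kept, a real deficit in group 1 shrinks towards zero, and that favours the claim. PPBC, OABSS, flow rate and residual urine are taken at the same late V3. The week-4 diary has the same exposure, and LOCF can make it the endpoint for patients who leave after V2.

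**Working it through.** **The plan's own figure.** Inputs from section 10.1: margin 0.80, SD 2.56 per group, 128 per group, alpha 0.05, true difference 0. A noncentral t calculation at one-sided 0.05 gives power 0.8019, matching the printed 0.80191. Inflating 128 for 10% drop-out gives 143 per group, 286 in total. The sample size reproduces, and the point does not depend on it.

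**Day count.** Take V1 as day 0, first dose that night, and every dose taken.
- First prescription: 28 nights, 0 to 27. Second, if V2 is on day 28: 56 nights, 28 to 83. Total 28 + 56 = 84.
- Windows counted from V1: V2 on days 21-35, V3 on days 77-91.
- The diary for a visit on day v covers days v−3 to v−1. A day is uncovered if no tablet was prescribed for the night before. With the last dose on night 83, day 84 is covered and day 85 is not.

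| V3 on day | Diary days | Uncovered |
|---|---|---|
| 85 | 82-84 | none |
| 86 | 83-85 | 1 |
| 87 | 84-86 | 2 |
| 88 | 85-87 | 3 |
| 91 | 88-90 | 3 |

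**Early V2.** With V2 on day 21 and leftover tablets unused, the second prescription ends on night 21 + 55 = 76. A V3 on days 79-91 then has an uncovered diary day, and an on-time V3 on day 84 (diary days 81-83) has all three uncovered.

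**Late V2.** The first prescription ends on night 27, so V2 on days 30-35 leaves at least one week-4 diary day uncovered and V2 on days 32-35 leaves all three. V2 on day 35 also moves the end of the second prescription to night 35 + 55 = 90, which covers every permitted V3 diary.

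**All permitted combinations.** There are 15 × 15 = 225. Let j be the V2 shift in days.
- *Leftovers used.* Each of the 8 values j ≤ 0 gives 6 V3 days with some uncovered diary and 4 with all three uncovered. For j = 1 to 5, the counts with some uncovered fall 5, 4, 3, 2, 1. For j = 1 to 3, the counts with all uncovered fall 3, 2, 1. Totals: 48 + 15 = **63** and 32 + 6 = **38**.
- *Leftovers unused.* The counts are 6 − j and 4 − j where positive. Totals: 13 + 12 + … + 1 = **91** and 11 + 10 + … + 1 = **66**.

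These count calendar combinations. They are not shares of patients.

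**Effect on the comparison (illustration only).** Assume the same share f of each group loses a fraction g of its change, with SD unchanged. A true deficit of 0.80 then appears as 0.80 × (1 − f·g). SE = 2.56 × √(2/128) = 0.32. The chance of a false claim with a 95% confidence interval is 1 − Φ(1.96 − (0.80 − apparent deficit)/0.32).

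| f, with g = 1 | Apparent deficit | False claim |
|---|---|---|
| 0 | 0.80 | 1 − Φ(1.960) = 2.5% |
| 5% | 0.76 | 1 − Φ(1.835) = 3.3% |
| 10% | 0.72 | 1 − Φ(1.710) = 4.4% |
| 20% | 0.64 | 1 − Φ(1.460) = 7.2% |

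If only half the effect is lost (g = 0.5), 10% affected gives 0.76 and 3.3%, and 20% gives 0.72 and 4.4%.

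**The case against.** A reader might infer that fully compliant patients with a late visit have no tablets left. The protocol does not say so. It gives prescription durations, not tablet counts, and neither states nor excludes an overage. Missed doses would leave spare tablets. Three months, read as calendar months of about 90 days, would largely close the gap at V3. This stands: the finding is about what the stated durations imply, not about what was dispensed.

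A reader might also take 6 of 15 permitted V3 days as 40% of patients. That does not follow. Section 3 offers the window as an exception for when it is needed, and a late V2 moves the second prescription later.

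Nor do the documents support total loss of effect. Section 4.6.1 sets a 14-day wash-out for prohibited drugs, including other anticholinergics, whereas the uncovered days in the main case fall 2 to 7 days after the last dose. With no placebo arm, part of the change from baseline may not depend on the drug at all. The bias towards zero also assumes similar shares affected in the two groups; unequal shares could push it either way.

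The week-4 route is narrow: it needs a late V2 followed by drop-out, with drop-out planned at 10%. Adverse events are recorded at V2 and V3 whatever the supply. If section 7.4 is taken literally, V3 falls on days 49-63 and the V3 gap disappears, although that contradicts week 12 everywhere else. Finally, a sensitivity analysis may already be in the statistical analysis plan, which is not at hand.

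What survives is the mismatch itself: the fixed durations, the windows and the diary rule, each as written, do not fit together.

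**Conclusion.** The point holds as an inconsistency of moderate weight. On the stated durations, with V2 on day 28, a V3 on days 86-91 puts at least one primary diary day beyond the prescribed treatment, and a V3 on days 88-91 puts all three there. An early V2 with leftovers unused widens the gap; a late V2 moves the problem to the week-4 diary. This rests on week 12 as the V3 date, a nightly dose from day 0, full compliance and no overage.

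The consequence for the trial's conclusion cannot be sized from the documents. A false-claim rate of 3.3% to 7.2% instead of 2.5% belongs to assumed shares of 5% to 20% with complete loss of effect in both groups, and is smaller if the loss is partial. The documents do not support the stronger conclusion that the week-12 comparison as a whole is measured off drug or is invalid.

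**What to change.** Reconcile five items: the prescription durations in sections 7.2 and 7.3; the three-month and 12-week wording; the ±7-day windows, including whether they run from V1 or between visits; the diary timing; and the V3 date in section 7.4. Every permitted V2 and V3 diary day should then lie within the prescribed treatment period. Which passage gives way is for the sponsor and investigators to decide.

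Use the drug-intake dates already confirmed at V2 and V3 to flag diaries recorded after the last dose. Report the primary comparison without them as a sensitivity analysis, unless the statistical analysis plan already does so. Keep the primary endpoint as it is: restricting it to treated days is a debatable change that this finding does not require.

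The cost is a short amendment and one derived flag, plus either slightly more drug supplied or slightly less freedom in visit dates. The sensitivity set will be somewhat smaller than the main one.
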